## Abstract

**Background:** The increasing use of telemedicine in surgical care has shown promise in improving patient outcomes and optimizing healthcare resources. Surgical site infections (SSIs) are a major cause of healthcare-associated infections (HAIs), leading to significant economic and health burdens. A pilot study already demonstrated that RedScar© achieved 100% sensitivity and 83.13% specificity in detecting SSIs. Patients reported high satisfaction regarding comfort, cost-effectiveness, and reduced absenteeism. **Methods:** This multicenter prospective study will include 168 patients undergoing abdominal surgery. RedScar© utilizes smartphone-based automated infection risk assessments without clinician input. App-based detection will be compared with in-person evaluations. Sensitivity and specificity will be analyzed using receiver operating characteristic (ROC) analysis, while secondary objectives include assessing patient satisfaction and standardizing telematic follow-up. **Results:** This study aims to evaluate the efficacy of the RedScar© app, sensitivity, specificity in detecting SSIs. Satisfaction regarding comfort, cost-effectiveness, and absenteeism due to telematic detection and the monitoring of SSIs will be recorded too. **Conclusions:** This study seeks to validate RedScar© as a reliable and scalable tool for postoperative monitoring. By improving early SSI detection, it has the potential to enhance surgical recovery, reduce healthcare costs, and optimize resource utilization.

## 1. Introduction

Telematic follow-up in surgery has experienced significant growth, driven by technological advancements and social distancing measures stemming from the COVID-19 pandemic. Telemedicine offers numerous benefits, including remote consultations, preoperative evaluations, postoperative monitoring, and tele-mentoring, achieving high levels of user satisfaction [1,2]. The evolution of telemedicine has been marked by significant milestones in infection management, from early antiseptic techniques to modern digital monitoring tools. The ability to remotely assess surgical site infections (SSIs) represents a crucial advancement in preventing complications and optimizing healthcare resources.

Infections at the surgical site (SSI) represent the second most frequent type of healthcare-associated infection (HAI), comprising 19.6% of all HAIs across Europe [3]. Surgical site infections (SSIs) notably contribute to morbidity, leading to extended post-operative hospitalizations, the need for additional surgical interventions, higher mortality rates, and a negative impact on patients’ health-related quality of life (HRQoL) [4]. Recent epidemiological data indicate that SSI incidence varies between 0.5% and 10.1%, with higher rates in complex procedures. Additionally, 60% of SSIs are diagnosed post-discharge, emphasizing the importance of remote monitoring solutions [5,6].

In many cases, SSIs are diagnosed late, often after the patient has been discharged [6]. This delay exacerbates patient distress and significantly increases healthcare expenditures. In Europe, SSIs impose a considerable financial burden, with direct costs per infection estimated between EUR 10,443 and EUR 19,638 [7]. A comprehensive review highlights that these costs result from prolonged hospitalization, additional treatments, and outpatient visits. Furthermore, indirect costs—such as work absenteeism and long-term disability—pose further challenges to healthcare sustainability [8]. The early and effective detection of these infections post-discharge can prevent severe complications and optimize healthcare resources [9].

Several studies have explored the use of mobile applications for the telematic detection of SSIs. Some applications utilize thermal cameras to identify increases in temperature associated with infections [10], while others employ dressings monitored via mobile apps to detect or prevent infections at early stages [11]. However, these technologies are often complex and not widely applicable outside of research settings. The emergence of artificial intelligence (AI) and machine learning algorithms has opened new possibilities for SSI detection, with studies reporting predictive capabilities even before clinical symptoms appear [12]. Despite this progress, challenges related to cost, accessibility, and implementation hinder widespread adoption in clinical settings [12]

The RedScar© application v1.9 (Compilation 23) (University of the Balearic Islands, Palma, Spain) is designed to operate simply using a patient’s mobile phone and an internet connection, offering advantages over existing applications. Unlike previous studies that require the external evaluation of wound images [13].

The RedScar© app employs a comprehensive approach to assess surgical wound infections by integrating patient-reported data with automated image analysis. The user-friendly interface includes a structured questionnaire covering key wound-related factors such as pain severity (measured via a visual analog scale, VAS), redness, burning sensation, wound leakage, swelling, liquid secretion, and fever. Patients must complete all questions before proceeding to the next step, which involves uploading a wound photograph. Once submitted, the app initiates a multistep computerized image analysis process based on fuzzy sets and gray-scale mathematical morphology [14] which is then extended to color images [15]. By combining image analysis with questionnaire responses, RedScar© autonomously generates a diagnosis without requiring direct supervision from healthcare professionals. Developed in Java SE 11 (Oracle, Austin, TX, USA) using the Android Studio environment, RedScar© integrates advanced image-processing techniques through Python-based (Python 3.7, Python Software Foundation, Wilmington, DE, USA) repositories which localizes surgical staples and the wound in an image and reconstructs images.

RedScar© is fully automated, providing infection risk assessments without clinician input. Its independence from human intervention enhances scalability and cost-effectiveness in postoperative telemonitoring [16]. Utilizing real-time image processing and interactive questionnaires, RedScar© enables continuous patient engagement and rapid infection detection, potentially lowering rates of severe complications and hospital readmissions [17]. Previous studies have demonstrated that telemonitoring in surgery is feasible and can reduce the need for outpatient care while improving patient experiences [17,18,19].

The RedScar© Pilot Study [17]: Phase I/IIa evaluated the application for detecting and monitoring potentially infected surgical wounds. Among the 47 patients included, 41 successfully completed both remote and in-person follow-ups. The RedScar© system achieved a sensitivity of 100% for SSI detection, with a specificity of 83.13%. Patient satisfaction with telemonitoring was notably high: 97.6% considered it cost-effective, 90.47% believed it helped prevent absenteeism from work or school, and 80.9% found it a convenient option. While this pilot study confirmed the safety and feasibility of telematic follow-up using RedScar©, the low incidence of wound infections highlights the need for a multicenter trial to validate these findings and ensure standardized implementation across different healthcare centers. Our research aims to continue developing RedScar© as a user-friendly, reproducible tool to assist patients in managing surgical wounds at home, thus optimizing available resources.

## 2. Objectives

### 2.1. Primary Objectives

The primary objective will be to assess the sensitivity and specificity of the RedScar© application for detecting wound infection, comparing the app with in-person diagnosis. The ROC curve will be used to analyze the overall performance of the app and identify the optimal cut-off for the “Red Proportion” (maximizing sensitivity and specificity).

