### 3.6. Visit Schedule

The patient will be discharged after surgery when deemed appropriate by the attending physician.

They must download the RedScar© app before discharge so they can be taught how to use it correctly, and any questions regarding the app’s questionnaire will be addressed. Detailed explanations will be provided about changes in the wound, such as swelling, increased temperature, etc. As stated earlier, the inability to understand these conditions or use the app is a reason for exclusion.

The patient will attend their first follow-up at the surgical outpatient clinic on day 5 post-surgery to assess the wound and again on day 8 to remove staples and check the wound’s condition. Prior to the consultation, the patient will need to take a photograph of the wound using the app (on postoperative days 5 and 8) so the app’s results can be compared with the investigator’s in-person evaluation (Figure 1).

If a wound infection is suspected, the patient will need to visit the outpatient clinic or hospital emergency department (depending on the investigator’s guidelines) to be assessed by the main investigators or, if unavailable, by the attending nurse. They will confirm the presence or absence of wound infection, document it in the patient’s medical record, and perform the initial treatment. Additionally, the patient will be given a conventional follow-up appointment with the surgery clinic, as is performed for patients not included in this study.

At the end of the follow-up, patient satisfaction will be evaluated using the Telemedicine Satisfaction Questionnaire (Table 1) developed and validated by Yip et al. [2], which has been used in similar studies [17,18].

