### 4.2. Statistical Analysis

Data will be entered into data entry programs that ensure the integrity of the information. For this, programs that comply with data validation guidelines and software published by regulatory agencies will be used. The analysis plan will be prepared before the database is closed.

Quantitative variables will be analyzed descriptively using means and standard deviations or medians and percentiles, accompanied by a bilateral 95% confidence interval and range (minimum and maximum) or P50 [P25–P75]. Qualitative variables will be summarized in a table with both absolute and relative frequencies. Statistical significance will be assessed at *p* < 0.05. Data analysis will be conducted using IBM^®^ SPSS^®^ Statistics 19 software.

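### The primary objective mixes two index tests: the app's own diagnosis, and a 'Red Proportion' cut-off chosen in the same patients, whose apparent sensitivity would be too high

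*Protocol article*

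**What the plan says.** Section 2.1 (Primary Objectives) sets out to "assess the sensitivity and specificity of the RedScar© application for detecting wound infection, comparing the app with in-person diagnosis". Its next sentence gives the ROC curve two jobs: "The ROC curve will be used to analyze the overall performance of the app and identify the optimal cut-off for the" Red Proportion, chosen to maximise sensitivity and specificity. The Abstract (Methods) puts it more broadly: "Sensitivity and specificity will be analyzed using receiver operating characteristic (ROC) analysis".

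The Introduction describes a test that already yields a result: "By combining image analysis with questionnaire responses, RedScar© autonomously generates a diagnosis without requiring direct supervision from healthcare professionals". Section 3.1 has the app give a recommendation to the patient while the investigator assesses the wound for comparison. Section 3.6 has photographs taken on days 5 and 8 "so the app’s results can be compared with the investigator’s in-person evaluation". Section 3.2 sizes the study on kappa, with 15% infected by in-person assessment and 20% by the app.

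On timing, section 4.2 says: "The analysis plan will be prepared before the database is closed". The Abstract's conclusion presents the study as a validation of the app.

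**The concern.** Two tests sit inside one primary objective. The first is the app's delivered diagnosis, which combines image analysis with the questionnaire. The second is a threshold on Red Proportion that does not yet exist and is to be found by maximising sensitivity and specificity in the study data. The article does not define Red Proportion. Its name suggests an image feature, and if that is right, a threshold on it is a different test from the diagnosis the patient receives.

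The ambiguity matters because the two tests have different statistical properties. Accuracy of a rule fixed in advance carries no selection bias. Accuracy at a cut-off picked because it looked best in the same patients is too favourable. The excess falls on the smaller group, here the infected, and so on sensitivity. For an app meant to work without clinician input, an overstated sensitivity means that missed infections are understated.

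**Working it through.** **1. What the sample size presupposes.** Inputs from section 3.2: kappa 0.8, prevalences 0.15 and 0.20, precision 0.12, 95% confidence.

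- Chance agreement: 0.15 × 0.20 + 0.85 × 0.80 = 0.71.
- Observed agreement: 0.71 + 0.8 × (1 − 0.71) = 0.942.
- Both positive: (0.942 − 1 + 0.15 + 0.20)/2 = 0.146.
- n = z² × V / d², with V the Fleiss-Cohen-Everitt large-sample variance of kappa (0.6274): 3.8415 × 0.6274 / 0.0144 = 167.4, rounded up to **168**. The stated figure reproduces.
- 168 × 1.1 = 184.8, the stated **185**.

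This calculation needs a yes/no result from the app. It implies a sensitivity of 0.146/0.15 = 97.3% and a specificity of 0.796/0.85 = 93.6% for that result. It does not concern a cut-off still to be found.

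**2. Number infected.** At the planning prevalence, 168 × 0.15 = 25.2, about 25. At 10.1%, the upper end of the incidence range in the Introduction, 168 × 0.101 = 17.0.

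**3. Optimism of a cut-off chosen in the sample.** Assumptions: one reading per patient; the marker is normal with equal variance in both groups; the mean difference is √2 × Φ⁻¹(AUC). The article gives no AUC, so a range is used. In each of 4,000 simulated studies of 168 patients, the cut-off maximising sensitivity + specificity was chosen. The sensitivity seen in that sample was then compared with the true sensitivity at the same cut-off.

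| AUC (assumed) | 25 infected: apparent vs true | Excess | 17 infected: apparent vs true | Excess |
|---|---|---|---|---|
| 0.70 | 0.709 vs 0.615 | 9.4 points | 0.728 vs 0.609 | 11.9 points |
| 0.80 | 0.775 vs 0.695 | 8.0 | 0.790 vs 0.684 | 10.5 (from unrounded values) |
| 0.90 | 0.859 vs 0.790 | 6.8 (from unrounded values) | 0.868 vs 0.776 | 9.1 (from unrounded values) |
| 0.95 | 0.912 vs 0.852 | 6.0 | 0.920 vs 0.841 | 7.9 |
| 0.98 | 0.952 vs 0.901 | 5.1 | 0.958 vs 0.892 | 6.6 |

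The excess in specificity in these runs is 0.3 to 1.1 points. Placing the cut-off midway between neighbouring observed values, instead of at one of them, raises this to at most about 2 points and lowers the sensitivity excess by less than one point.

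**4. The alternative.** For a rule fixed before the data are seen, the selection excess is zero by construction. What remains is sampling error. With 25 infected, the exact 95% interval for sensitivity is 86.3% to 100% if all 25 are detected, and 74.0% to 99.0% if 23 are.

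**The case against.** The strongest reply is that the article already provides for the right analysis. The first sentence of section 2.1 concerns the application as such. Sections 3.1 and 3.6 compare the app's results with the investigator's assessment, section 3.2 presupposes a binary app output, and the Introduction names the version (v1.9, Compilation 23). On this reading the Red Proportion search is an extra.

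Much of this stands, and it limits the point. A reader might infer that the primary sensitivity and specificity are certain to be those at the new cut-off, or that the app's own diagnosis has been dropped. The article says neither. A reader might also take it as established that Red Proportion is only one component of the app; it is undefined, so that is an inference. Nor can it be said that selection will go uncorrected, since an optimism correction could be in an analysis plan that is not shown. Writing that plan before database closure is not an error in itself.

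The magnitude is conditional too. It applies only if accuracy at the new cut-off is reported, it rests on an assumed AUC and marker distribution, and it ignores the second reading per patient.

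The reply does not remove the ambiguity. The cut-off search is part of the primary objective, the ROC curve is said to show the app's overall performance, and the Abstract offers ROC analysis as the only route to sensitivity and specificity. Someone following that route as written could report a biased estimate for a test other than the one the app delivers.

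**Conclusion.** The point holds as an unresolved choice of index test in the primary objective, with a bias of predictable direction if the choice falls one way. If accuracy at the re-derived cut-off is reported, sensitivity is overstated by about 5 to 9 points at the planned prevalence (25 infected) and about 7 to 12 points with 17 infected. Specificity is overstated by about 1 to 2 points or less. This assumes a binormal, equal-variance marker with AUC between 0.70 and 0.98 and one reading per patient. If the primary figures are those of the app's own fixed output, this bias does not arise. The documents do not settle which it will be, and a study presented as a validation should.

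**What to change.** - In section 2.1, state that primary sensitivity and specificity are those of the app's own locked output (v1.9, with its existing threshold) against the in-person diagnosis, from the 2x2 table with exact 95% confidence intervals. Align the Abstract's sentence on ROC analysis with this.
- Define Red Proportion. Label its ROC curve and cut-off search secondary or exploratory.
- Report accuracy at the new cut-off only with optimism correction, using a bootstrap that re-selects the cut-off in every resample, or state that it needs validation in new patients.
- Settle all of this before app results and in-person results are linked, not merely before database closure.

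The cost is a few sentences and a short bootstrap script, with no extra patients or visits. The downside is that the corrected sensitivity at the new cut-off will be several points lower than the uncorrected one.

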### 2.2. Secondary Objectives

The secondary objectives will be to verify the standardization of surgical wound follow-up using the RedScar© app across different centers and to assess the satisfaction level of subjects undergoing telemedicine-based follow-up using a validated telemedicine satisfaction questionnaire.

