**Figure 3 jcm-14-02210-f003:**
[figure not shown]
Examples of images that are expected to be included in this study, taken by patients in the preliminary phase of this study (see the RedScar© Pilot Study [15]).

**Table 1 jcm-14-02210-t001:** Satisfaction questionnaire [2].

Satisfaction Questionnaire	Answer
1. The information received before participating in this study was adequate.	Yes/No
2. I do not have difficulties with the questionnaire used within the application.	Yes/No
3. I do not have difficulties when taking the photo and uploading it to the mobile application.	Yes/No
4. I have spent less time with telematic follow-up than with personal revision.	Yes/No
5. I think that telematic follow-up is cheaper than the personal revision.	Yes/No
6. I think that telematic review could prevent absenteeism from work/school.	Yes/No
7. Telematic follow-up seems more comfortable to me than follow-up in consultations.	Yes/No
8. I think that telematic monitoring could detect a bad evolution earlier.	Yes/No
9. I think the healthcare provided via telemedicine is consistent.	Yes/No
10. The care received seems adequate to me.	Yes/No
11. Overall, I am satisfied with the quality of service being provided via telemedicine.	Yes/No
12. I would prefer telematic follow-up to face-to-face consultations.	Yes/No
13. I will use telemedicine services again.	Yes/No
14. Following the instructions of the application, have you checked your wound at your health center?	Yes/No, Why?
15. Although the application had ruled out the infection of the wound, have you preferred to check it in person?	Yes/No, Why?
16. Despite using the application, have you consulted any other source (Google-type web search, opinion of close relatives)?	Yes/No, Why?
17. How do you think we can improve the RedScar© application? Leave your comment.	

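### Table 1 is called validated although at least six of its 17 items are written for this app, and items 14 and 15 do not exclude the scheduled clinic visits

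*Protocol article*

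**What the plan says.** Section 2.2 lists satisfaction with telemedicine follow-up as a secondary objective, to be measured "using a validated telemedicine satisfaction questionnaire". Section 3.6 names the instrument and its origin: "patient satisfaction will be evaluated using the Telemedicine Satisfaction Questionnaire (Table 1) developed and validated by" the authors of a cited study. It adds, of the same instrument, "which has been used in similar studies". Neither section says that the list was adapted.

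Table 1 has 17 items. Items 1 to 13 are answered Yes or No, items 14 to 16 add a request for the reason, and item 17 is an open comment. Three examples show the app-specific content:

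- Item 3: "I do not have difficulties when taking the photo and uploading it to the mobile application".
- Item 15: "Although the application had ruled out the infection of the wound, have you preferred to check it in person".
- Item 17: "How do you think we can improve the RedScar© application".

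Section 3.6 also has every patient seen at the surgical outpatient clinic on postoperative days 5 and 8, whatever the app reports. The abstract announces that "Satisfaction regarding comfort, cost-effectiveness, and absenteeism due to telematic detection" will be recorded.

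**The concern.** Validation belongs to a particular set of items with a particular response format. If items are added or rewritten, the property has to be shown again or claimed only for the part left unchanged. Here the label covers all of Table 1, so the results could be reported as validated satisfaction when part of the list has no validation described.

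Items 14 and 15 raise a separate difficulty. They appear to be meant to show whether patients acted on the app's advice, and whether they trusted a negative result. In this design every patient is examined in person anyway. Unless the items set those examinations aside, the answers may reflect the visit schedule instead of the patient's reaction to the app.

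Finally, cost-effectiveness is a technical term. If it is attached to an opinion item, a reader of the results could take a percentage of agreement for economic evidence.

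**Working it through.** The plan states no target, score or precision for satisfaction, so there is no figure to reproduce. Its computed sample size (168, or 185 with the allowance for losses, in section 3.2) concerns agreement between app and clinic and does not enter this point. The check is a reading of sections 2.2, 3.6 and 4.1, the abstract and Table 1 against each other.

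**Step 1: sort the items of Table 1 by content.**

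| Content | Items | Count |
|---|---|---|
| Refers to this application or its use | 2, 3, 14, 15, 16, 17 | 6 |
| Refers to information given about the study | 1 | 1 |
| Worded for telematic follow-up, telemedicine or care in general | 4 to 13 | 10 |

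The total is 6 + 1 + 10 = 17. The app-specific share is 6/17 = 35%. If item 1 is counted as added for this study, the share is 7/17 = 41%. Because item 1 is arguable, six is the figure to rely on.

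**Step 2: compare with the label.** An item that names RedScar, or asks about uploading a wound photograph, cannot be assumed to carry the validation of a general telemedicine questionnaire. Section 3.6 offers the cited validation and prior use in similar studies. Prior use is not validation, and the article describes no validation of the app-specific items. For items 4 to 13 the document does not show whether wording or response format match the source.

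**Step 3: compare items 14 and 15 with the visit schedule.** Take a patient whose app result is negative on days 5 and 8 and who attends both visits. The app has ruled out infection, and the wound has been checked in person. Asked item 15, this patient may answer Yes because the check took place, or No because attending was not a matter of preference. Both answers are reasonable, and they describe the same behaviour. Item 14 has the same gap: a patient told by the app to seek review may have been seen at a visit that was due in any case. Neither item mentions the scheduled visits.

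**Step 4: trace cost-effectiveness to its source.** The only item in Table 1 about cost is item 5, a Yes/No opinion that remote follow-up is cheaper. It does not set cost against any effect. Section 4.1 lists no cost variable. The introduction uses the same label for the pilot, where 97.6% of patients held that opinion. Since no scheduled visit is replaced by the app in this trial, the answer is also partly hypothetical.

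**The case against.** The strongest reply is that most of Table 1 is generic and does measure satisfaction. Item 11 asks about overall satisfaction, and items 7, 10, 12 and 13 cover comfort, adequacy, preference and willingness to use telemedicine again. This stands. A reader might infer that the whole questionnaire was made up for this study and measures nothing validated. The document does not support that: ten items are general in wording, and the cited source is not available for comparison.

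A second reply is that items 14 and 15, read literally, exclude scheduled visits, because a mandatory visit is neither an act on the app's instruction nor a preference. Item 14 speaks of the health center, while scheduled visits are at the surgical clinic, and section 3.6 provides for an extra visit when infection is suspected. Both items also ask for the reason. This stands in part. Careful respondents may read the items so, and the reasons will resolve some answers, but nothing in the wording secures it. What fails is the inference that nearly all patients would answer Yes. The document gives no basis for predicting the split.

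A third reply concerns the comparative items. A reader might infer that the compulsory visits confound all of them. They do not: in the paired design each patient experiences both forms of follow-up, so comfort and preference (items 7 and 12) can be answered from experience.

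Fourth, a reader might infer that the trial claims to establish cost-effectiveness. It does not. The objectives contain no economic endpoint, and the abstract lists the term as a satisfaction topic. The absence of cost data is therefore no fault; only the label is.

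**Conclusion.** The point holds as a minor one, in three parts:

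- The validated label is not shown to apply to at least 6 of 17 items (35%), and its reach over the others cannot be established from the document.
- Two items, 14 and 15, cannot reliably separate a reaction to the app from scheduled attendance.
- One opinion item is carried under the name cost-effectiveness.

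The effect on the reported percentages cannot be quantified from the document. The conclusion assumes that Table 1 as printed is the questionnaire to be given to patients, and that no validation of this adapted list exists elsewhere; if one does, citing it would settle the first part. Satisfaction is a descriptive secondary endpoint, so the accuracy analysis and the sample size are untouched.

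**What to change.** - **Sections 2.2 and 3.6.** Describe Table 1 as a questionnaire adapted from the general instrument. Limit the word validated to items taken unchanged from it, mark those items in the table, and report them separately from the added app-specific items.
- **Items 14 and 15.** Before the questionnaire is used, reword both to ask only about visits other than those scheduled for days 5 and 8. This has to come first, because ambiguous answers cannot be repaired at analysis.
- **Abstract and results.** Call item 5 patient-perceived cost in place of cost-effectiveness.

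The cost is a weaker label for the endpoint and slightly less comparability with the pilot on two items. No change to the design, the number of patients or the primary analysis is needed.
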